### 3.11.4. Statistical Analysis Plan

The study results are mainly analyzed by descriptive statistics. The measurement data will be expressed as mean, standard deviation, median and maximum and minimum values, and the enumeration data and ranked data will be presented as frequency (composition ratio), rate and confidence interval.

The two-tailed test will be used for all statistical tests. When the P-value is 0.05 or lower, the difference will be considered statistically significant. The confidence interval adopts 95% confidence level.

1) Basic characteristics of patients

2) Efficacy analysis

The corresponding 95% CIs of ORR and DCR are calculated based on the Clopper-Pearson exact method. The Kaplan-Meier method will be used to estimate the median of the DOR, PFS and OS, and to draw the survival curve.

3) Safety evaluation

Safety evaluation is mainly based on descriptive statistical analyses, and lists the adverse events and adverse reactions occurring in this trial (adverse reactions are defined as adverse events that are 'definitely related/probably related/possibly related to' the test drugs"). The laboratory examination results describe the circumstances that are normal before the trial but abnormal after the treatment, as well as their relationships with the test drugs when abnormal changes occur.

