# PROTOCOL SYNOPSIS

| **Study Drug** | Apatinib plus Capecitabine |
| --- | --- |
| **Study Title** | A Phase II Study to Evaluate the Efficacy and Safety of Apatinib in Combination with Capecitabine in Patients with Recurrent/Metastatic Nasopharyngeal Carcinoma Who Failed Platinum-based Therapies |
| **Investigator** | [name]; [name] |
| **Protocol Version** | 2.2 |
| **Protocol Date** | October 29, 2018 |
| **Study Design** | A non-randomized, open-label, single-arm exploratory study |
| **Study Properties** | A clinical study initiated by the investigator |
| **Study Subjects** | Patients with recurrent/metastatic advanced nasopharyngeal carcinoma (NPC) who failed platinum-based therapies |
| **Study Objective** | To evaluate the efficacy and safety of apatinib combined with capecitabine in the treatment of patients with recurrent/metastatic advanced NPC who failed platinum-based therapies |
| **Study Sample Size** | This study is a superiority trial using Simon's two-stage design to estimate the sample size. Alpha is 0.05, Beta is 0.2, and the testing power is 0.8. According to literature, the ORR of capecitabine monotherapy is 24.2%, assuming that the ORR of the combination of apatinib and capecitabine increases by 15%, i.e., ORR = 39.2%, and the drop-out rate of 10%, at least 64 cases are needed. In the first stage, 31 cases will be enrolled, when the number of effective cases is less than 8, it is considered that the efficacy of the drug combination is not better than the monotherapy, and the trial will be terminated. Otherwise, continue to the second stage of enrollment. |

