## 3.3. Sample Size Estimation

This study is a superiority trial using Simon's two-stage design to estimate the sample size. One-sided alpha is 0.05, beta is 0.2, and the testing power is 0.8. According to literature, the ORR of capecitabine monotherapy is 24.2%, assuming that the ORR of the combination of apatinib and capecitabine increases by 15%, i.e., ORR = 39.2%, given a 10% drop-out rate, at least 64 cases are needed. In the first stage, 31 cases will be enrolled, when the number of effective cases is ≤ 7, it is considered that the efficacy of the drug combination is not better than the monotherapy, and the trial will be terminated. Otherwise, continue to the second stage of enrollment.

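### Section 3.3 sizes the trial for a one-sided 0.05 test, but section 3.11.4 makes all tests two-tailed at 0.05 without exempting the primary ORR; if 3.11.4 governs, power is about 74%, not 80%

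*Protocol*

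**What the plan says.** Protocol section 3.3 calls the trial a superiority trial with a Simon two-stage design and sets the error rates: "One-sided alpha is 0.05, beta is 0.2, and the testing power is 0.8". It takes a null ORR of 24.2% (capecitabine alone) and a target of 39.2%. After the allowance for dropout it concludes: "given a 10% drop-out rate, at least 64 cases are needed". The first stage enrols 31 patients, and the trial stops if 7 or fewer respond.

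The synopsis gives the same figures without a side: "Alpha is 0.05, Beta is 0.2, and the testing power is 0.8".

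Section 3.11.4 sets the rule for inference: "The two-tailed test will be used for all statistical tests". A P-value of 0.05 or lower counts as significant, and confidence intervals are at the 95% level. On the primary endpoint it adds: "The corresponding 95% CIs of ORR and DCR are calculated based on the Clopper-Pearson exact method". It does not exempt the ORR from the two-tailed rule.

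**The concern.** A one-sided test at 0.05 and a two-tailed test at 0.05 are different tests. For a gain in ORR, the two-tailed test puts roughly half as much error in the upper tail, so it needs more responses to succeed. The 80% power in section 3.3 belongs to the one-sided rule only.

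At stake is the primary conclusion. For some response counts the two sections give opposite answers on the same data, and the protocol does not say which prevails. If that is settled only after the responses are known, the choice of rule can follow the result.

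**Working it through.** **Inputs.** From section 3.3: p0 = 0.242, p1 = 0.392, one-sided alpha 0.05, power 0.80, first stage n1 = 31 with stopping at r1 = 7 or fewer, 10% dropout, total 64. From section 3.11.4: two-tailed 0.05 and the 95% Clopper-Pearson interval.

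**Formula.** With a final cut-off of c responses among n patients, the probability of declaring success at true rate p is

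S(p) = Σ (x = 8 to 31) P(X1 = x) × P(X2 ≥ c − x), with X1 ~ Bin(31, p) and X2 ~ Bin(n − 31, p).

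Alpha is S(0.242) and power is S(0.392).

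**Step 1: reproduce the plan's figure.** An exact search for alpha ≤ 0.05 and power ≥ 0.80 gives 58 as the smallest total. Among the solutions with 58, the one with the smallest expected size under the null is n1 = 31, r1 = 7, success at 20 or more of 58. Its alpha is 0.0495 and its power 0.8002. The first stage matches section 3.3 exactly. Adding 10% gives 58 × 1.1 = 63.8, rounded up to 64, as stated. The sizing is therefore the one-sided minimax design.

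**Step 2: judge the design's own boundary by section 3.11.4.** For 20/58 (34.5%):
- two-sided exact binomial p against 24.2% = 0.090 (0.102 by doubling the upper tail);
- 95% Clopper-Pearson interval 22.5% to 48.1%, which includes 24.2%.

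So 20/58 is a success under the design and not significant under section 3.11.4.

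**Step 3: power if section 3.11.4 governs (7/31 stopping rule kept).**

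| Analysed | Criterion | Responses needed | Power |
|---|---|---|---|
| 58 | one-sided design rule | 20 | 0.800 |
| 58 | two-sided exact p ≤ 0.05 (21/58: p = 0.045) | 21 | 0.720 |
| 58 | lower 95% Clopper-Pearson limit above 24.2% (22/58: 25.5%) | 22 | 0.625 |
| 64 | either two-tailed criterion (23/64: p = 0.040, lower limit 24.3%) | 23 | 0.739 |

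The shortfall is 80.0 − 73.9 = 6.1 points at 64. At 58 it is 80.0 − 72.0 = 8.0 or 80.0 − 62.5 = 17.5 points.

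**Step 4: one-sided cut-offs for the number analysed.** The smallest c with exact alpha ≤ 0.05, stopping rule kept:

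| Analysed | Cut-off | Alpha | Power |
|---|---|---|---|
| 58 | 20 | 0.0495 | 0.800 |
| 59 | 21 | 0.032 | 0.752 |
| 60 | 21 | 0.039 | 0.780 |
| 61 | 21 | 0.046 | 0.806 |
| 62 | 22 | 0.030 | 0.760 |
| 63 | 22 | 0.036 | 0.787 |
| 64 | 22 | 0.042 | 0.811 |

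**The case against.** The best defence is that section 3.11.4 was never meant to judge the ORR. It describes the analysis as mainly descriptive, names no test of ORR against 24.2%, and asks only for an interval. A Simon design decides by a response count and is one-sided by construction, so the two-tailed sentence may be a general default. This stands in part: the loss of power is conditional on 3.11.4 governing the ORR decision. It does not remove the contradiction. The sentence covers every test without exception, and section 3.3 presents a superiority trial with an alpha and a power, which implies a decision on ORR.

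It is also fair that 62.5% is the extreme case. The synopsis defines the ITT population as all enrolled, and section 3.11.3 keeps every patient who took the drug at least once. The denominator should therefore lie nearer 64 than 58, where the shortfall is about 6 points. Nor does any section require the lower 95% limit to exceed 24.2%.

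Three stronger readings may tempt a reader, and the document does not support them:
- **That 64 is too few.** It reproduces, with 80.0% power, under the rule it was calculated for.
- **That the unstated final cut-off is itself the fault.** A separate statistical analysis plan may give it, the stated inputs lead to it, and its absence does not lower power.
- **That the type I error exceeds 11%.** Requiring only 20 responses among 64 would give alpha 0.113, but the protocol states no such rule.

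**Conclusion.** The point holds as an internal contradiction. Section 3.3 fixes a one-sided 0.05 test and section 3.11.4 a two-tailed 0.05 test, and nothing says which applies to the primary ORR. The calculation of the sample size is correct. If section 3.11.4 applies, the 80% power stated in 3.3 and the synopsis becomes about 74% with 64 analysed, and 72.0% or 62.5% with 58, depending on the two-tailed criterion. The result at the design boundary, 20/58, reverses.

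These figures assume true rates of 24.2% and 39.2%, the 7/31 stopping rule applied as written, and final p-values and intervals computed as for a single-stage binomial sample.

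**What to change.** In section 3.11.4, exempt the primary ORR test from the two-tailed sentence. State that ORR ≤ 24.2% is tested one-sided at 0.05 by the two-stage rule, and that the 95% Clopper-Pearson interval is descriptive. Add the side of alpha to the synopsis.

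State the final cut-off for the number actually analysed: at least 20 of 58, at least 21 of 59 to 61, or at least 22 of 62 to 64. Each keeps exact alpha at or below 0.05. Power is 80.0% at 58, 80.6% at 61 and 81.1% at 64, and about 75% to 79% at 59, 60, 62 and 63, so this should be acknowledged.

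If the sponsor prefers the two-tailed rule, keep 64 and restate the power in section 3.3 and the synopsis as about 74%.

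Either way the cost is wording in sections 3.3 and 3.11.4 and the synopsis, with no extra patients. It should be settled before the final response data are seen.

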| **Study Statistical Methods** | Efficacy evaluation:  The 95%CI of ORR and DCR are calculated based on the Clopper-Pearson exact method.  The Kaplan-Meier method is used to estimate the median DOR, PFS and OS, and survival curves will be created.  Safety evaluation:  Safety evaluation is mainly based on descriptive statistical analyses and lists the adverse events and adverse reactions occurring in this trial (adverse reactions are defined as "adverse events that are 'definitely related/probably related/likely related to' the test drugs"). The laboratory examination results describe circumstances that are normal before the test but abnormal after the treatment, as well as their relationships with the test drugs when an abnormal change occurs. |

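### The primary ORR gets only a fixed-sample, two-sided 95% interval, which matches neither the two-stage sampling nor the one-sided 5% level used to size the trial

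*Protocol*

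**What the plan says.** Protocol section 3.3 (Sample Size Estimation) names the design: "This study is a superiority trial using Simon's two-stage design to estimate the sample size". It sets the error rates: "One-sided alpha is 0.05, beta is 0.2, and the testing power is 0.8". The reference rate is given as "According to literature, the ORR of capecitabine monotherapy is 24.2"%, and the target and total follow: "i.e., ORR = 39.2%, given a 10% drop-out rate, at least 64 cases are needed". The interim rule reads "In the first stage, 31 cases will be enrolled, when the number of effective cases is ≤ 7", in which case the trial ends. No final success count is printed, and no number of evaluable patients before the dropout allowance.

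The analysis text is separate. Section 3.11.4 says "The corresponding 95% CIs of ORR and DCR are calculated based on the Clopper-Pearson exact method", and the synopsis (Study Statistical Methods) says "The 95%CI of ORR and DCR are calculated based on the Clopper-Pearson exact method". Section 3.11.4 also makes every test two-tailed at 0.05, sets the confidence level at 95%, and describes the analysis as mainly descriptive. Neither place mentions the two stages.

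**The concern.** Clopper-Pearson is exact for one binomial sample of fixed size. Here the sample size depends on the data: the trial ends at 31 or goes on. The alpha and power in section 3.3 are properties of that two-stage process at a one-sided level. The one method fixed for the primary endpoint uses neither the process nor the level.

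At stake is the reading of a borderline result. The protocol calls the trial a superiority trial against 24.2% and prints no final boundary, so readers will set the reported interval against 24.2%. A count that the design treats as success could then be published with an interval that includes the reference rate.

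**Working it through.** **Inputs** (section 3.3): p0 = 0.242, p1 = 0.392, one-sided alpha 0.05, power 0.80, n1 = 31, stop at r1 = 7 or fewer, total 64 with 10% dropout. From section 3.11.4: Clopper-Pearson, 95%, two-tailed.

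**Step 1: reproduce the design.** With final size n, the probability of success at k or more responders is

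P(k; p) = Σ over x = 8 to 31 of Pr[Bin(31, p) = x] × Pr[Bin(n − 31, p) ≥ k − x].

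A search over all two-stage designs gives, as the one with the smallest n, 7/31 then 19/58: success at 20 or more of 58, alpha 0.0495, power 0.8002. The probability of an early stop is 51.4% at p0. Dropout: 58 × 1.1 = 63.8, rounded up to the stated 64 (58/0.9 = 64.4 would give 65). So n = 58 and k = 20 are well supported, but they are inferred.

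**Step 2: compare methods at n = 58.** The fixed-sample p-value is Pr[Bin(58, 0.242) ≥ k]. The Clopper-Pearson lower limit is the α/2 quantile of Beta(k, 59 − k). Power is P(k; 0.392), with the stage 1 stop in force.

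| Responders | Two-stage p | Fixed-sample p | 90% lower limit | 95% lower limit | Power if this is the boundary |
|---|---|---|---|---|---|
| 20 | 0.0495 | 0.0508 | 24.16% | 22.49% | 80.0% |
| 21 | 0.0270 | 0.0274 | 25.70% | 23.99% | 72.0% |
| 22 | 0.0137 | 0.0138 | 27.26% | 25.51% | 62.5% |

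- The planned 95% interval first excludes 24.2% at 22.
- **Change of level alone:** a two-stage test at one-sided 2.5% also needs 22 (0.0270 at 21, 0.0137 at 22). The mismatch of level is therefore enough by itself to move 20 to 22.
- **Ignoring the stages alone:** at one-sided 5%, the boundary moves from 20 to 21, with power 72.0%.

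**Step 3: how far this depends on n = 58.** Section 3.11.3 analyses every patient dosed at least once, so the final n may be as high as 64. There, at one-sided 5%, both methods need 22 (p = 0.0420 and 0.0434, power 81.1%). For final n from 54 to 64, the one-sided boundaries of the two methods differ only at 58. The mismatch of level remains at 64: the 95% lower limit is 22.95% at 22 and 24.32% at 23, so 23 are needed and power is 73.9%.

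**Step 4: bias of the raw proportion** (responders divided by patients, averaged over both ways of ending, minus the true rate; n = 58):

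| True ORR | Bias, percentage points |
|---|---|
| 24.2% | −1.4 |
| 26% | −1.4 |
| 32% | −1.0 |
| 39.2% | −0.3 |

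**Step 5: coverage of the 95% Clopper-Pearson interval over the two-stage sample space** (n = 58). It is 97.5% at 24.2% and 95.3% at 39.2%. The minimum is 93.9%, at a true ORR of 41.1%, where the upper limit falls below the truth 4.0% of the time against a nominal 2.5%. Values under 95% occur only in narrow bands between 37.5% and 44.9%. The lower limit exceeds the truth no more than 2.5% of the time over true rates of 15% to 50%. With n = 64 the minimum is 94.1%.

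**Step 6: the matching analysis at 20 of 58.** Solving P(20; p) = 0.05 and P(21; p) = 0.95 gives a two-stage 90% interval of 24.22% to 46.2%, which agrees with p = 0.0495. With t = 20 and n2 = 27, the UMVUE is Σ C(30, x − 1)·C(27, t − x) ÷ Σ C(31, x)·C(27, t − x), both sums over x = 8 to 20. This gives 35.0%, against a raw 34.5%.

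**The case against.** The protocol never says that success is judged by a Clopper-Pearson limit. It calls the analysis mainly descriptive, and its one printed decision rule, the stage 1 stop, is a count that the interval does not touch. If the final decision is also made by counting responders, an interval reported beside it leaves the power at 80%. This stands, so the 62.5% is conditional on the interval being read as the test.

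A reader might also infer that the choice of Clopper-Pearson moves the boundary from 20 to 21 and cuts power to 72%. The documents do not support this as a general statement. Those figures belong to a one-sided 5% (90% interval) reading that the protocol does not plan, and they arise at n = 58 but at no other final n from 54 to 64. At the stated 95% level the two methods need the same 22.

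Nor does the interval simply cover less than 95%. Coverage exceeds 95% at both design rates, the shortfall is at most 1.1 points, and the error that would favour an efficacy claim stays within its nominal 2.5%.

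Finally, estimators are often left to a statistical analysis plan, and one may exist. Here, though, the protocol itself fixes the method, twice, so the method can be checked against the design.

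**Conclusion.** The point holds as a mismatch between design and analysis. The only inference planned for the primary endpoint uses neither the sampling scheme nor the level from which section 3.3 takes its alpha and power. Under the inferred design, 20 and 21 of 58 are successes whose planned interval still contains 24.2%.

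Most of the possible loss of power (80.0% to 62.5% at n = 58, 81.1% to 73.9% at n = 64) comes from one-sided 5% against two-sided 95%. Ignoring the stages adds a small downward bias and the loss of guaranteed 95% coverage, and it moves the one-sided boundary at n = 58 but not at 64. Those stage-related effects alone would be minor. The correction is worth making because it concerns the primary endpoint and costs almost nothing.

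The result assumes that the final n and boundary are 58 and 20, and that readers compare the interval with 24.2%.

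**What to change.** In section 3.11.4 and the synopsis:

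1. State that the final ORR decision follows the two-stage boundary. Print the evaluable n and the success count (20 of 58, if the sponsor confirms the reconstruction), and say how the boundary is reset if the analysed n differs.
2. Take the ORR p-value and a two-sided 90% interval from the two-stage sampling distribution, using a stage-wise ordering such as Koyama-Chen. Exempt this test from the general two-tailed rule, so that it matches the one-sided 5% in section 3.3.
3. Report the UMVUE beside the raw proportion.
4. Keep Clopper-Pearson for DCR and, if wanted, as a 95% interval for ORR labelled descriptive.

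Items 1 and 2 belong together. A two-stage 95% interval would still need 22 of 58, and a 90% Clopper-Pearson interval would still need 21. The cost is a few sentences and a few lines of code, with no extra patients or data.

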| **Drug Dosing and Administration Regimen** | Apatinib Mesylate Tablets 500 mg, po, qd, q4w, plus Capecitabine tablets 1000 mg/m^2^, po, bid, d1-14, q3w (take the medicine at the same time every day as possible);  A treatment cycle lasts 3 weeks, and the combined medication will be continued until the occurrence of toxicity intolerance, disease progression, or death, or patients refuse to continue participating in this clinical study, or the investigators determine that the medication must be terminated. |
| **Study Efficacy Evaluation** | **Intent-to-Treat (ITT) Population**: The ITT population is defined as all subjects who are enrolled.  **Per Protocol (PP) Population**: The per protocol population (PP) defines as a subset of the subjects who meet all of the trial criteria and are compliant with the protocol and absence of any major protocol violations.  The efficacy is assessed by imaging examinations and the RECIST 1.1 criteria will be employed:  **Primary efficacy indicators:** Objective response rate (ORR) of tumor  **Secondary efficacy indicators:**   1. Disease control rate (DCR) 2. Duration of response (DoR) 3. Patient's progression-free survival (PFS) 4. Overall survival (OS)   5) Safety and tolerance of the regimen |
| **Study Safety Evaluation** | All the patients that have received the treatment with the test drugs for at least one cycle, and have safety records will be taken as an effective population for safety analysis. The abnormal values of patients' physical examination results, vital signs, adverse events and laboratory examinations will be summarized. Adverse events will be reported and classified according to the Common Terminology Criteria for Adverse Events (CTCAE) Version 4.0 of the NCI. |

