## 3.4. Criteria for Inclusion, Exclusion and Withdrawal of subjects

### 3.4.1. Inclusion Criteria

1) Patients with histologically proven recurrent and/or metastatic NPC;

Patients with recurrent and/or metastatic NPC shall meet any of the following: 1. Recurrence after radiotherapy; 2. Metastasis

2) Patients who have failed the platinum-based therapy and received at least first-line platinum-containing chemotherapy;

3) Male or female patients: aged 18-70 y/o;

4) ECOG Performance Status score: 0-2;

5) The estimated survival is ≥ 3 months;

6) Patients not receiving chemotherapy or radiotherapy 4 weeks before the inclusion;

7) With at least one measurable lesion according to the RECIST criteria (the size measured with B-mode ultrasound, MRI or spiral CT scan is ≥ 10 mm and the measurable lesion has not received any radiotherapy);

8) Patients whose major organs function well, i.e., to meet the following requirements 1 week before the inclusion:

a. Blood routine examination:

i. Hemoglobin > 80 g/L (no blood transfusion within 14 days);

ii. Neutrophil count > 1.5 × 10^9^/L;

iii. Blood platelet count > 80 × 10^9^/L;

b. Biochemical examination:

i. Total bilirubin ≤ 1.5 × ULN (upper limit of normal);

ii. ALT or AST ≤ 2.5 × ULN (upper limit of normal);

iii. Creatinine < 2.0 times the ULN, endogenous creatinine clearance rate > 50 ml/min (Cockcroft-Gault Equation);

9) Females of child-bearing age must undergo a pregnancy test (serum or urine) 7 days before the inclusion, with a negative result and a willingness to take reliable contraceptive methods during the trial;

10) Subjects voluntarily participate in the study, sign the Informed Consent form, and are well compliant and cooperative in follow-ups.

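### The laboratory summary is worded as normal-to-abnormal shifts, so worsening from an abnormal baseline that eligibility permits falls outside it

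*Protocol*

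**What the plan says.** The rule appears twice. Section 3.11.4, item 3 (safety evaluation) says: "The laboratory examination results describe the circumstances that are normal before the trial but abnormal after the treatment". The synopsis, under Study Statistical Methods, says: "The laboratory examination results describe circumstances that are normal before the test but abnormal after the treatment". Both go on to mention the relationship of such changes to the study drugs. Neither mentions CTCAE grade, or a value that was already abnormal and became worse.

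The synopsis row on Study Safety Evaluation is broader. It lists abnormal values from several sources and ends with "laboratory examinations will be summarized". It sets no condition on the baseline value, and it grades adverse events by CTCAE 4.0.

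Section 3.4.1, item 8 sets the entry limits. They include "Blood platelet count > 80 × 10^9^/L" and "Creatinine < 2.0 times the ULN", and also haemoglobin above 80 g/L, total bilirubin up to 1.5 × ULN and ALT or AST up to 2.5 × ULN. Section 3.8.1 admits patients with 24-hour urine protein below 1 g.

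**The concern.** A normal-to-abnormal description suits a population that enters with normal laboratory values. This one need not: the patients have failed platinum-based therapy, and the entry limits deliberately allow mild abnormalities. For a parameter that is abnormal at entry, no later value can satisfy the first half of the rule, however bad it becomes.

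The rule is also ungraded. ALT moving from 0.9 to 1.1 × ULN qualifies, while ALT moving from 2 to 15 × ULN does not. The description can therefore show trivial shifts and leave out serious ones.

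Safety and tolerance are a secondary objective (Section 2.2). The parameters affected are ones for which the Protocol gives toxicity guidance: proteinuria (3.7.2), bone marrow suppression (3.7.7) and hepatic impairment (3.7.9). A laboratory summary is useful because it gives a check that does not depend on whether an investigator chose to report a value as an adverse event. As worded, that check is missing for patients who start from an abnormal value.

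**Working it through.** The Protocol gives no laboratory toxicity rate and no share of patients with abnormal baselines, so there is no figure to reproduce. The check is a comparison of the texts, followed by an illustration.

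**Step 1: does eligibility admit abnormal baselines?**

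| Parameter | Entry limit | Abnormal value admitted? |
|---|---|---|
| Total bilirubin | up to 1.5 × ULN | Yes, between 1 and 1.5 × ULN |
| ALT or AST | up to 2.5 × ULN | Yes, between 1 and 2.5 × ULN |
| Creatinine | below 2.0 × ULN | Yes, between 1 and 2 × ULN, subject to the clearance limit |
| Urine protein | 24-hour value below 1 g | Yes; the table in 3.7.2 counts (+), or a 24-hour value below 1.0 g, as grade 1 |
| Haemoglobin | above 80 g/L | Yes, if the laboratory's lower limit of normal exceeds 80 g/L |
| Platelets | above 80 × 10^9/L | Yes, if the lower limit of normal exceeds 80 × 10^9/L |

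The first four follow from the Protocol itself. The last two rest on the stated condition about the reference range, which the Protocol does not give but which is not in real doubt.

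**Step 2: does worsening from such a baseline meet the rule?** Take an example built only from the Protocol's figures. A patient enters with urine protein (+), grade 1 in the 3.7.2 table, and later reaches 3.5 g in 24 hours, grade 3 in the same table. The value was not normal before treatment, so the change is outside the description in 3.11.4. The same patient still counts for any other parameter that was normal at entry, so the exclusion is per parameter, not per patient.

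**Step 3: do the statements agree?** The Study Safety Evaluation row would include this patient's value; the Study Statistical Methods row and 3.11.4 would not. The synopsis alone would give two different laboratory tables.

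**Step 4: illustration of size.** Every input is assumed except 64, the planned size in Section 3.3. Let b be the share with an abnormal baseline for one parameter, and g_n and g_a the grade 3-4 risks with normal and abnormal baselines.

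- Full rate = (1 − b) × g_n + b × g_a
- Rate shown over all patients = (1 − b) × g_n

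For b = 0.4, g_n = 0.10 and g_a = 0.20:

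- Full = 0.6 × 0.10 + 0.4 × 0.20 = 0.14, and 64 × 0.14 = 9.0 patients.
- Shown = 0.6 × 0.10 = 0.06, and 64 × 0.06 = 3.8 patients.

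| b | Shown (g_n = 10%) | Full, g_a = 10% | Full, g_a = 20% |
|---|---|---|---|
| 20% | 8% (5.1 patients) | 10% (6.4) | 12% (7.7) |
| 40% | 6% (3.8) | 10% (6.4) | 14% (9.0) |
| 60% | 4% (2.6) | 10% (6.4) | 16% (10.2) |

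**Step 5: dependence on the denominator.** The Protocol fixes no denominator for this description. If only patients with a normal baseline are counted, the rate shown is g_n = 10% throughout. With equal risks that equals the full rate and nothing is understated as a rate, although the events in the other patients remain absent. With g_a = 20% and b = 0.4 it is 10% against 14%.

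**The case against.** A reader might infer that these patients can never be scored, even at grade 3-4, and that the trial's laboratory toxicity is therefore understated. The Protocol does not support that.

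- The sentence says that the results describe normal-to-abnormal changes. It does not say that nothing else will be shown.
- Section 3.9.4.1 includes abnormal laboratory findings in the definition of an adverse event, with no baseline condition. Section 3.9.4.2 requires abnormal laboratory data to be recorded in the CRF and followed up. Adverse events are graded by CTCAE 4.0 and listed under 3.11.4 itself, and 3.9.4.3 takes all subjects in the safety evaluation as the denominator for adverse reactions.
- Section 3.11.4 also promises means, medians and extremes for measurement data, which could display a very high or low laboratory value whatever the baseline.
- Sections 3.7.2 and 3.7.9 link grade 3 proteinuria and grade 3/4 transaminase and bilirubin elevation to suspension of treatment, and 3.6 requires suspensions to be stated in the final report.
- A shift table is the kind of detail often left to a statistical analysis plan, which is not at hand.

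Most of this stands, and it limits the point to the laboratory summary. It does not remove it. Recording a value in the CRF is not tabulating it. The adverse-event listing depends on the investigator's decision to report. A maximum or minimum does not say how many patients worsened. As to a separate analysis plan, the point is not that detail is missing. A restrictive rule is written twice, and a plan that follows the Protocol would inherit it.

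**Conclusion.** The point holds for the laboratory summary as worded. For each parameter with a permitted abnormal baseline, worsening, including to grade 3-4, is outside the description in 3.11.4 and in the synopsis's statistical methods, and the rule conflicts with the broader statement in the Study Safety Evaluation row.

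The size of the shortfall is unknown. The 6% against 14% example depends on the assumed 40% share, the assumed risks of 10% and 20%, and the use of all 64 patients as denominator. It also supposes that grade would be tabulated within the normal-to-abnormal group, which the rule does not require. It measures what one summary would show, not what the trial can report. Nor do the documents establish that patients with abnormal baselines carry a higher grade 3-4 risk; that too is an assumption.

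The primary endpoint and the stage-one stopping rule are untouched. Severity is minor to moderate.

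**What to change.** In Section 3.11.4, item 3, and in the synopsis under Study Statistical Methods, replace the normal-to-abnormal sentence with wording such as:

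*For each laboratory parameter, baseline CTCAE 4.0 grade will be tabulated against worst on-treatment grade for all patients in the safety analysis set. The number with a worsening of at least one grade, and the number with a new or worsened grade 3-4 value, will be reported whatever the baseline grade.*

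Align the synopsis row on Study Safety Evaluation with this text, so that the three places describe the same summary.

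The cost is small. Blood counts, biochemistry and urine tests are already scheduled at baseline (3.8.1) and at the end of each cycle (3.8.2), so nothing more is asked of patients. The work is one more table per parameter. The downside is that reported laboratory toxicity may look higher than under the present wording.
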